### Statistical analyses

All data analysis will be carried out according to a pre-established analysis plan. The primary analysis will be intention-to-treat. Two sided significance tests will be used. Power calculations will be conducted on all parametric analyses. Only findings with power > 80%, CI = 95% and ά < 0.05 will be determined to be statistically significant. Differences between the intervention and comparison groups in the proportion of mothers using nursing, medical, other health, parental support and child care services will be analysed using contingency tables. Descriptive analyses will be undertaken of critical events such as death or child removal as the incidence of these events is low in the Australian population. Impact and outcome data collected at multiple time points will allow imputation of missing data for participants who did not complete every data point using appropriate techniques [24,25]. Child development and parent-child interaction measures, and quality of the home environment (HOME inventory) will be analysed cross-sectionally at each collection point. All other impact and outcomes measures will be analysed cross-sectionally at 1, 12 and 24 months, to estimate the prevalence of each impact and outcome, their association with demographic and risk factors, and differences between the intervention and comparison groups using contingency tables for non-parametric data and t-tests for parametric data. Longitudinal analyses will then be undertaken to compare differences in outcomes over time between the intervention and comparison groups using Repeated Measures ANOVA for parametric data and Friedmans two-way ANOVA for non-parametric data.

A priori subgroup analyses will be conducted using General Linear Modelling to assess differences between the intervention and comparison groups in impact and outcomes for: first-time mothers compared with mothers with two or more children; Australian born mothers compared with mothers born overseas; mothers with only one risk factor compared with mothers with multiple risks at the time of recruitment antenatally; and mothers with lower psychosocial resources due to probable distress at the time of recruitment (EDS score of 10 or more) compared with mothers with higher psychosocial resources for parenting (EDS score of 9 or less).

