### Sample Description

During the recruitment period 847 pregnant women from the 2168 postcode area were identified. Of these women, 509 were excluded from the study because they did not meet the eligibility criteria: no risk factors (n = 338), required an interpreter (n = 98), no telephone (n = 33), no data provided to the SRO (n = 40). From the eligible population (n = 338), another 130 were excluded for reasons such as refusal to participate, non-contactable or maternal and/or foetal death.

Two hundred and eight (208) women were recruited to participate in the study and were randomly assigned to the intervention (n = 111) and comparison group (n = 97). The baseline demographic and risk characteristics of the trial groups are detailed in Tables 1 and 2. At an average of 27.7 years, the mothers in the sample were slightly younger than mothers who gave birth in NSW in 2005 (29.9 years), however, their age was similar to mothers from the most disadvantaged quintile (28.0 years) [23]. A considerably larger proportion of women in the sample were born in an overseas country (49.0%), most of whom were born in a non-English speaking country, compared with mothers birthing in NSW in 2005 (27.9% born overseas) [31].

**Table 1 T1:** Baseline maternal demographic characteristics of trial groups

**Characteristic**	**Intervention Group (n = 111)**	**Comparison Group (n = 97)**
Mean age ± SD	27.6 ± 6.7	27.7 ± 5.9

Parity, n (%)		

0	31 (27.9)	34 (35.1)

≥ 1	80 (72.1)	63 (64.9)

Country of birth, n (%)		

Australia	56 (50.5)	50 (51.5)

Overseas	55 (49.5)	47 (48.5)

Marital status, n (%)*		

Married/living with partner	87 (80.6)	79 (84.9)

Single/separated/divorced	21 (19.4)	14 (15.4)

Level of education, n (%)†		

High school/vocational	88 (83.0)	74 (80.4)

Degree or higher	18 (17.0)	18 (19.6)

Main source of household income, n (%)†		

Full or part-time wages	73 (68.9)	66 (72.5)

Benefit or pension	33 (31.1)	25 (27.5)

Housing tenure, n (%)§		

Own or purchasing	47 (46.1)	43 (50.6)

Renting or other	55 (53.9)	42 (49.4)

* Seven women did not disclose their marital status

† Eleven women did not disclose their level of education or source of income

§ Twenty one women did not disclose their housing tenure

**Table 2 T2:** Baseline maternal risk characteristics of trial groups

**Characteristic**	**Intervention Group (n = 111)**	**Comparison Group (n = 97)**
Age < 19 years, n (%)	7 (6.3)	7 (7.2)

Unsupported parent, n (%)	4 (3.6)	0 (0.0)

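### Friedman's test has no study-arm term, so the planned over-time comparison of the arms is not delivered for non-parametric outcomes

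*Protocol article*

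**What the plan says.** The Statistical analyses section of the protocol article sets out two layers of analysis for most outcomes.

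- **Cross-sectional.** "All other impact and outcomes measures will be analysed cross-sectionally at 1, 12 and 24 months", with the arms compared "using contingency tables for non-parametric data and t-tests for parametric data".
- **Longitudinal.** "Longitudinal analyses will then be undertaken to compare differences in outcomes over time between the intervention and comparison groups", and the methods follow at once: "using Repeated Measures ANOVA for parametric data and Friedmans two-way ANOVA for non-parametric data".

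Child development, parent-child interaction and HOME are handled separately: "quality of the home environment (HOME inventory) will be analysed cross-sectionally at each collection point". No other longitudinal method is named for non-parametric data. The design is two independent randomised arms, 111 and 97 women (Sample Description).

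**The concern.** The stated purpose is a comparison between arms, and the two named methods are offered as counterparts for it. They are not counterparts. Repeated Measures ANOVA can carry arm as a between-woman factor and test arm by time. The two ways in Friedman's test are already used up by woman (the block) and occasion (the repeated condition), which leaves no place for arm.

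An analyst who follows the text would obtain, for each non-parametric outcome, a p-value for change over time. Over the first two years of life many outcomes could change in both arms whatever the intervention does. Such a p-value could be reported as evidence about the programme, while a real difference between the arms in how an outcome develops could go unseen.

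**Working it through.** The article gives no figure to reproduce here. The check is on the structure of the test, followed by simulations whose effect sizes are assumptions.

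**Inputs.** Three occasions, k = 3 (1, 12 and 24 months, Statistical analyses). This assumes that the longitudinal analysis uses the same occasions as the cross-sectional one; the structural argument does not depend on k. Sizes are 75 per arm (Sample size) or 111 and 97 (Sample Description). Tests are two-sided at 0.05.

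**1. The statistic.** With n women, let R_j be the sum over women of the within-woman rank at occasion j:

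Q = 12 / [n k (k+1)] × Σ R_j² − 3 n (k+1), referred to chi-square on k − 1 = 2 degrees of freedom. The 5% critical value is −2 ln(0.05) = 5.99.

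Only within-woman ranks appear. If a woman's values are (a, b, c), then (a+d, b+d, c+d) has the same ranks for any d. A constant difference between arms therefore cannot alter Q. Numerically, Q was 0.760 before and 0.760 after 5 SD was added to every value in one arm.

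**2. Arms moving in opposite directions, 75 per arm, n = 150.** Every intervention woman is ranked 1, 2, 3 and every comparison woman 3, 2, 1.
- R_1 = 75×1 + 75×3 = 300; R_2 = 75×2 + 75×2 = 300; R_3 = 300.
- 12/(150×3×4) = 1/150, and 3×150×4 = 1,800.
- Q = (3 × 300²)/150 − 1,800 = 1,800 − 1,800 = **0**.

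With 111 and 97 women, n = 208:
- R_1 = 111 + 3×97 = 402; R_2 = 2×208 = 416; R_3 = 3×111 + 97 = 430.
- The deviations from 416 are −14, 0 and 14, so Q = (14² + 14²)/208 = 392/208 = **1.88**, still below 5.99.

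**3. Both arms identical, all 150 women ranked 1, 2, 3.** The rank sums are 150, 300 and 450. Q = (22,500 + 90,000 + 202,500)/150 − 1,800 = 2,100 − 1,800 = **300**, the largest value possible, with no difference between arms.

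**4. Less extreme cases.** Simulation with 75 per arm, three occasions, a coarse ordinal score, within-woman correlation 0.5 and 1,500 runs. The correlation and the effects are assumptions. A Mann-Whitney test on change from first to last occasion serves as a simple between-arm yardstick; it targets change only.

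| Assumed truth (SD units) | Pooled Friedman rejects | Mann-Whitney on change rejects |
|---|---|---|
| No effect | 6.0% | 5.6% |
| Constant arm difference 0.5 | 6.1% | 5.0% |
| Same trend 0/0.25/0.5 in both arms | 99.7% | 5.3% |
| Opposite trends, change differs by 0.5 | 4.9% | 82.9% |
| Intervention improves by 0.5, comparison flat | 66.9% | 84.1% |

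In the last row Friedman often rejects, but only because the average over both arms moves. The result cannot be told apart from a common trend.

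A second set of assumptions (woman and residual SD both 1, 2,000 runs) gave 5.5% rejection for a constant arm shift of 1.0. It gave 73% for a common trend of 0/0.2/0.4 with no arm effect. The rejection rate under a common trend thus ranges from 73% to 99.7% across the two sets.

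**5. Other ways of running it.** With time as the block and arm as the column, the test needs matched observations, whereas the arms are independent and unequal in size, and the same women recur in every block. For binary outcomes Friedman's test reduces to Cochran's Q, which is also purely within-woman.

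**The case against.** **The arms are still compared on these outcomes.** This stands and limits the point. A reader might infer that any real arm difference becomes invisible. The documents do not support that, because contingency tables compare the arms at each of 1, 12 and 24 months, and service use is compared the same way. A constant arm difference, to which Friedman is blind, is one that those tables could show.

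**Few headline outcomes are touched.** This largely stands. Of the outcomes named under Sample size, HOME and the Bayley scale fall under the cross-sectional rule. SF-12 is sized by a standardised effect and so would plausibly go to Repeated Measures ANOVA. The rates of immunisation, injury and breast-feeding have contingency tables; the defect reaches them only if they are also analysed longitudinally.

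**The separate analysis plan may settle it.** The section refers to a pre-established plan that is not shown. But the article does not leave the choice open: it names a test and the job that test is to do, and the two do not match.

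Three further inferences are tempting but go too far.

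- *Loss of incomplete records.* Friedman's test needs every occasion, but the same section plans imputation for women who missed some, so this is not a separate defect.
- *Misreading a result that is significant in one arm only.* Nothing says that the test will be run by arm. How often the arms would disagree also depends on the assumed trend: 50% in the second simulation. In the first, the arms rejected in 93.5% and 93.8% of runs, so disagreement is about 0.935×0.062 + 0.065×0.938 = 12%.
- *Scores forced into categories.* The article does not say that skewed or ordinal scores are what it calls non-parametric, and the figure listing the measures is not shown. Its talk of prevalence and rates suggests categorical variables, for which contingency tables are suitable.

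**Conclusion.** The point holds for the longitudinal between-arm comparison of non-parametric outcomes, and for nothing wider. Friedman's test has neither an arm term nor an arm-by-time term, so the analysis as written cannot answer the question set for it. A significant result would speak to change over time and not to the intervention.

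This conclusion rests on the formula and needs no assumed effect size: Q is unchanged by any shift of one arm, is 0 for fully opposed arms of 75, and is 300 for identical arms that share a trend. The rejection rates are illustrations that depend on assumed trends and correlations, and they do not predict this trial's results.

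The single-occasion comparisons, the parametric outcomes, and the measures assigned to cross-sectional analysis keep valid routes. Because the text states an unsuitable method and does not merely omit detail, it should be corrected before the longitudinal analyses are run.

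**What to change.** Replace Friedman's test in the longitudinal sentence with a method that contains arm, visit and arm-by-visit terms, and state which term or contrast answers the question:

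- binary outcomes: GEE or mixed logistic regression;
- ordinal or skewed scores: a mixed proportional-odds model, or a rank-based factorial method for longitudinal data.

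State as well which outcomes are classed as non-parametric and which of them enter the longitudinal analysis. If any ordinal or skewed scores are in that class, compare them at single time points with the Wilcoxon-Mann-Whitney test or proportional-odds regression, and keep contingency tables for categorical data.

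The cost is a change of wording and some analyst time with standard software. No new data, visits or participants are needed.

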### Data collection

Processes, impacts and outcomes were measured identically in both groups. The measures were consistent with the state-wide Families NSW (previously Families First) Outcomes Evaluation Framework [22]. Wherever possible, instruments had demonstrated validity and reliability and were chosen from those used in previous studies of home visiting or the NSW Health Child Health Survey [23]. Basic demographic data such as maternal age, country of birth, marital status, and parity were collected from the routine standardised hospital and community health data collections. The risk factors used to identify eligibility for the trial were recorded from the hospital obstetric database. These data were used to describe the sample. The number of home visits, early childhood health clinic visits and telephone consultations with early childhood nursing services, and the use of medical, other health, parental support and child care services was recorded from the routine community child health data collection and parental report. At each contact the occurrence of any of the following events was noted: maternal death, child death, child placement in out-of-home care. Impact and outcome measures are detailed in Figure 1.

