### Sample size

Funding allowed three nurses to be employed to deliver the intervention, each with a maximum caseload of 25 mothers (in accordance with NSW Department of Health guidelines). Hence, 75 families could be receiving intervention at any one time. Previous randomised controlled trials reported in the literature have had a median number of subjects of 65 per group (range 9–347). A sample size of 75 subjects per group has power of 0.80 at the 95% level to detect effect sizes of 0.5 or larger for the HOME Inventory, Bayley Scale of Mental Development and maternal health (SF-12), and detect differences of less than 22% in the rates of immunisation, child injury and breast-feeding. In systematic reviews of home visiting conducted by Elkan [12] and MacLeod [5] effects of at least these sizes were found in the HOME Inventory; a meta-analysis of trials using the Bayley Scales of Mental and Motor Development showed an overall effect size of 0.17, however, effect sizes were larger (up to 0.5 for mental development and 0.4 for motor development) in studies that assessed development at 12 months or later; the pooled odds ratio for immunisation and breastfeeding at 3 months were 1.40 and 1.34 respectively; the pooled odds ratio for reduction in child injury in studies aimed at improving a range of child and maternal health outcomes was 0.76; significant change in depression and stress scores were reported in studies using EDS and the Parenting Stress Index. Trials with fewer than 50 subjects have shown significant intervention effects in the quality of the home environment measured using the HOME inventory, child mental development measured using the Bayley Scale of Infant Mental Development, immunisation rates, possible maternal depression measured using the EDS, parenting stress measured using the Abidin Parenting Stress Index, and transition to solids [12]. Recruitment took place over the period February 2003 to March 2005. This allowed a planned recruitment of 90 subjects per group whilst maintaining the maximum intervention caseload of 75, to allow for a proposed 15% loss to follow-up.

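### One composite significance rule also governs four a priori subgroup contrasts for which the trial was not sized, and it serves them badly on each reading of its power clause

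*Protocol article*

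**What the plan says.** All of the decision wording is in the Statistical analyses section of the protocol article.

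- **Subgroups.** The plan states that "A priori subgroup analyses will be conducted using General Linear Modelling to assess differences between the intervention and comparison groups in impact and outcomes". Three of the contrasts begin "first-time mothers compared with mothers with two or more children; Australian born mothers compared with mothers born overseas; mothers with only one risk factor", the last of these being set against mothers with multiple risks. The fourth splits on the Edinburgh Depression Scale (EDS) at 10 or more against 9 or less. No measure or time point is singled out.
- **Decision rule.** "Only findings with power > 80%, CI = 95% and ά < 0.05 will be determined to be statistically significant". Tests are two-sided, and the section adds: "Power calculations will be conducted on all parametric analyses". Nothing says what effect the power refers to, or whether it is fixed in advance or computed from the result.
- **Measures.** The Data collection section says: "Impact and outcome measures are detailed in Figure 1". That figure is not readable here.
- **Size.** The Sample size section says: "A sample size of 75 subjects per group has power of 0.80 at the 95% level to detect effect sizes of 0.5 or larger". It names six outcomes: the HOME Inventory, the Bayley mental scale, the SF-12, immunisation, child injury and breast-feeding. It does not mention interactions.

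**The concern.** A rule written for the overall comparison of arms is carried over to subgroup contrasts that have much less information. The contrasts carry an a priori label and none is marked exploratory, so one that passes the rule would be reported as a pre-specified, significant finding.

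The programme is meant to inform service delivery. A subgroup result that is due to chance, or is much too large, could be read as showing that visiting works only for distressed or first-time mothers, and could affect who is offered it. The opposite failure is also possible: if the power clause is applied strictly, the contrasts may be unable to produce a significant finding at all.

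**Working it through.** **Inputs.** 75 per group and 0.5 SD (Sample size). 208 women randomised; parity 0 in 31 + 34 = 65; Australian born 56 + 50 = 106 (Table 1). Psychosocial distress 46 + 43 = 89 (Table 2, taken as EDS 10 or more). Participation 51.4% at 24 months (Discussion), so 0.514 × 208 ≈ 107 women. The split between one and multiple risks is not tabulated and is not computed.

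**The plan's own figure.** With 75 per group, the effect detectable with 80% power at two-sided 0.05 is (1.960 + 0.842) × √(2/75) = 0.457 SD, and power for 0.5 SD is 0.865. The stated 0.80 for 0.5 or larger holds as a bound. It concerns the overall effect only.

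**Precision of a subgroup contrast.** With equal arms, the interaction SE in SD units is 2/√(n·p·(1−p)), where p is the subgroup share. The detectable interaction at 80% power is 2.80 × SE.

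| Contrast | p | SE, n = 208 | Detectable | SE, n = 107 | Detectable |
|---|---|---|---|---|---|
| Parity 0 v 1 or more | 0.3125 | 0.299 | 0.84 | 0.417 | 1.17 |
| Australian v overseas born | 0.510 | 0.277 | 0.78 | 0.387 | 1.08 |
| Distressed v not | 0.428 | 0.280 | 0.79 | 0.391 | 1.10 |

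Power for a 0.5 SD interaction is 39% to 44% with 208 women (38% to 44% with the actual cell sizes) and 22% to 25% with 107.

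**Reading 1: design power, met for the overall effect, so the clause does not bite.** Each contrast is tested at 0.05. For one outcome at one visit, the chance of at least one false finding is 1 − 0.95⁴ = 18.5% if the contrasts are independent, and about 15.5% by simulation if their test statistics correlate at 0.5. If all six named outcomes are tested once each (24 tests), it is 1 − 0.95²⁴ = 70.8% if independent, about 53% with correlation 0.5 between outcomes and between contrasts, and about 38% with 0.8 and 0.5. More visits would raise these figures.

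**Reading 2: observed power.** Observed power exceeds 80% when |z| > 1.960 + 0.842 = 2.802, that is p < 0.0051. The chance of at least one false finding falls to about 2.0% for one outcome and 6% to 11% over six, on the same correlation range. But 2.802 SE is the detectable column above, so an estimate must exceed 0.78 to 0.84 SD (n = 208) or 1.08 to 1.17 SD (n = 107) to be declared. Relative to 0.5 SD, that is at least 0.78/0.5 = 1.6 times and up to 1.17/0.5 = 2.3 times. Any true interaction below these thresholds is overstated whenever it is declared.

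**Reading 3: design power for a 0.5 SD interaction.** Power is 22% to 44%, always below 80%, so none of the three computable contrasts can qualify, whatever the data show.

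**The case against.** The strongest case against the point has four parts.

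1. **The rule is stricter than plain 0.05.** General Linear Modelling is parametric and power is to be calculated for all parametric analyses, so the power clause does reach these contrasts. On the two readings that give it force, false findings are rare or impossible. This stands. A reader might infer that the plan will probably yield a false subgroup finding, but the documents do not support that. On reading 1, independent tests pass 50% only from 14 tests; on reading 2, only at about 136, or 34 outcome-by-time analyses per contrast.
2. **The number of tests is unknown.** That every measure is tested is an inference from unrestricted wording, because Figure 1 is not shown. If only the three parametric outcomes in the sample size section were tested (12 tests), reading 1 gives 46% if independent and 29% to 36% with correlation. This also stands.
3. **Multiplicity and labelling are commonly left to the analysis plan, which the article says exists.** True, and their absence alone would be no finding. But the article itself states the rule by which a finding "will be determined to be statistically significant" and makes no exception for subgroups. The point rests on that text.
4. **Limited power is partly disclosed.** The Discussion concedes reduced power for small and moderate effects. The figure of 107 women is the lowest participation point, before imputation, and record-based data cover the whole sample. This is fair, but the calculation with all 208 women already meets the same difficulty.

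A reader might also infer that a positive subgroup result is about as likely to be false as true. For a 0.25 SD interaction, power is 13% to 15% (n = 208) or 9% to 10% (n = 107). Equal odds then need a prior of 0.05/(0.05 + 0.15) = 25% to 0.05/(0.05 + 0.09) = 36% that the interaction exists. The documents give no prior, so the statement cannot be made.

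**Conclusion.** The point holds in a limited form. The article applies one composite rule to all findings, leaves the meaning of its power clause open, and includes four subgroup contrasts for which the trial was not sized. Each reading has its own failure:

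- **Clause does not bite:** error of 15.5% to 18.5% for one outcome, and 38% to 71% over six.
- **Observed power:** error of about 2% and 6% to 11%, but only very large estimates can be declared.
- **Design power for 0.5 SD:** contrasts that can never qualify.

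A chance or exaggerated subgroup effect can therefore be reported as a pre-specified significant finding. How probable that is cannot be settled from this document.

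The figures assume no true interactions for the error rates, equal arms, the Table 2 distress row as the EDS split, one visit per outcome, and six outcomes where stated. Naming one primary outcome would not remove the problem, since four contrasts on that outcome would still fall under the rule.

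**What to change.** In the Statistical analyses section, state that the four subgroup analyses are exploratory. Report each as one arm-by-subgroup interaction estimate with its 95% CI, exempt them from the statistical significance rule, and say that no claim of benefit in a subgroup will be made from them. This resolves the point on all three readings without having to decide what the power clause means for subgroups.

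The cost is one or two sentences of wording, with no new data or participants. The downside is that subgroup results can no longer be reported as significant findings.
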